## Abstract

**Background:** As the only traditional Chinese medicine injection approved by the China Food and Drug Administration for use as stroke first aid in ambulances, Xingnaojing Injection (XNJI) has been widely used in cases of both acute ischemic stroke (IS) and intracerebral hemorrhage (ICH). However, there is no robust clinical evidence regarding the efficacy and safety of the early use of XNJI during stroke first aid. The main purpose of this trial is to observe whether XNJI, intravenously administered within 24 h of onset in the prehospital ambulance setting, protects against early neurological deterioration (END) on the third day of onset in patients with acute stroke.

**Methods:** The Trial of a prehospital intervention with traditional Chinese medicine for acute stroke (TRACE) is a Mixed-Methods research (MMR) study that involves a combination of quantitative and qualitative research. The quantitative research part of this project is a prospective, multicenter, observational, clinical registry study, for which we aimed to recruit 1,000 patients with acute stroke (IS and ICH). Based on our observation of whether XNJI was intravenously administered within 24 h of onset in the prehospital ambulance setting, patients with acute stroke will be divided into two groups: the exposure group comprising patients who were intravenously administered XNJI and the nonexposure group comprising patients who were not. The primary outcome is early neurological deterioration (END) on the third day of onset defined as an increase of 2 or more points in the National Institute of Health Stroke Scale score between baseline and day 3. In addition, based on the aforementioned quantitative research, qualitative research will be conducted by interviewing emergency doctors about their knowledge and attitude regarding XNJI used for stroke first aid.

**Discussion:** The results of the TRACE study will provide preliminary evidence for the relationship between XNJI used within 24 h of onset and the presence of END on the third day after stroke onset; it will aid in improving the current knowledge regarding the early use of XNJI for stroke first aid.

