## Introduction

Stroke is the first cause of death and disability among adults in China and the second leading cause of death worldwide (Group, 2020). In 2019, among all the subtypes of stroke, ischaemic stroke (IS) had a prevalence of 62.4%, and intracerebral brain hemorrhage (ICH), of 27.9% (GBD 2019 Stroke Collaborators, 2021). Stroke, a life-threatening disease, often leads to severe central nervous system damage in case of untimely treatment (Saver, 2006; Chen et al., 2019). Early neurological deterioration (END) is a frequent and serious complication of acute stroke, with an incidence of 5%–40% (Thanvi et al., 2008; Geng et al., 2017). It is characterized by progressive deterioration of neurological function within 48-72 h after stroke (Celik et al., 2019; Kang et al., 2021). END is strongly associated with an increased risk of functional disability, mortality, and poor 3-month clinical outcomes (Kwan and Hand, 2006; Geng et al., 2017). Currently, vascular recanalization strategies, including intravenous thrombolysis (IVT) and endovascular therapy (EVT), are recommended first-line therapy options for acute ischemic stroke (AIS) (Ma et al., 2019; Powers et al., 2019). However, they only benefit a small number of patients due to narrow time windows, imaging dependence, high risk of bleeding, and limited repass rates (Wang et al., 2019). The treatment options for ICH are also limited (Schrag and Kirshner, 2020). There are no specific drugs for treating ICH, and the benefits and risks of surgical treatment are controversial (Deng and Wu, 2021; Zhang and Zhou, 2022)).

Xingnaojing injection (XNJI) is made using an extract from the An Gong Niu Huang pill, a popular and effective first-aid TCM used for acute stroke, which has been clinically applied for more than 200 years (Deng et al., 2010; Wang, 2022; Wang W. et al., 2022). Using modern pharmaceutical technology, dangerous ingredients, such as cinnabar and realgar, are removed, and four ingredients including musk, gardenia, Yujin, and borneol are retained and refined to obtain a convenient and effective water-soluble intravenous injection (Yue et al., 2019). Many studies have demonstrated the effectiveness and safety of XNJI for acute stroke (Ma et al., 2013; Shen et al., 2020; Wang et al., 2021), and the guidelines and consensus in China have recommended the use of XNJI as stroke first aid (Gao, 2016; Department of Neurology, 2018).

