Note: Field and variables not specifically specified will be applied to all acute stroke patients (IS and ICH). Abbreviations: TRACE, The Trial of a prehospital intervention with traditional Chinese medicine for acute stroke; ID, identity card; BEFAST, Balance-Eyes-Face-Arms-Speech-Time; XNJI, Xingnaojing Injection; NIHSS, National Institutes of Health Stroke Scale; BMI, Body Mass Index; CHD, Coronary Heart Disease; CT, Computed Tomography; MRI, Magnetic Resonance Imaging; ECG, electrocardiogram; mRS, modified Rankin Scale; ICH, intracerebral hemorrhage; GCS, Glasgow Coma Scale; TOAST, Trial of Org 10172 in Acute Stroke Treatment; IVT, intravenous thrombolytic therapy; EVT, endovascular treatment; TCM, traditional Chinese medicine; PT, Physical therapy; OT, Occupational therapy; ST, Speech training; BI, Barthel Index; AEs, Adverse Events.

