### Types of outcomes

#### Efficacy outcomes

The primary outcome is END on the third day of onset defined as an increase of 2 or more points in the NIHISS score between baseline and day 3. The secondary outcomes include the rates of stroke-related and any-cause deaths during hospitalization, differences in the changes in the neurological deficit degree, risk grade of ICH evaluated through changes in the ICH scale score from baseline to day 10 or the day of discharge, the proportion of patients with activities of daily living with a Barthel Index score of ≥90, and the proportion of independent patients defined by a modified Rankin Scale score ≤2 at 30 ± 3, 60 ± 3, and 90 ± 7 days after stroke onset. A complete list of the efficacy outcomes analyzed in the TRACE study is presented in Table 2.

**TABLE 2 T2:** | The complete list of efficacy outcomes analyzed in the TRACE study.

Primary outcome
1. Early neurological deterioration# change
Early neurologic deterioration (END) is defined as an increase of 2 points or more in the National Institute of Health Stroke Scale (NIHSS) score between baseline and 3 days. The NIHSS score ranges from 0 (best score) to 42 (worst score). [Time Frame: between baseline and 3 days]
Secondary outcomes
1. Rate of stroke-related deaths and deaths from any cause Rate of stroke-related deaths and deaths from any cause during hospitalization [Time Frame: during hospitalization] 2. Neurological deficit Comparison of the change of degree of neurological deficit evaluated by the NIHSS [Time Frame: baseline and day 10 or the day of discharge] 4. Risk grade of a cerebral hemorrhage Comparison of the change of risk grade of Intracranial hemorrhage evaluated by Intracerebral Haemorrhage (ICH) scale. The ICH score ranges from 0 (best score) to 6 (worst score). [Time Frame: baseline and day 10 or the day of discharge] 5. Activities of daily living Activities of daily living will be measured by Barthel Index (BI) score. The proportion of patients with a BI score of ≥ 90. The BI score ranges from 0 (worst score) to 100 (best score). [Time Frame: 30, 60, and 90 days] 6. The proportion of patients’ independent The proportion of patients’ independence is defined as a modified Rankin Scale (mRS) score of ≤ 2. The mRS score ranges from 0 (best score) to 6 (worst score). [Time Frame: 30, 60, and 90 days]

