
### Sample size calculation

According to the definition of the dominant population, at least one particular subgroup will have a positive outcome in terms of the primary efficacy index. A previous study conducted in Germany reported that approximately 13% of patients exhibited END on the third day after stroke onset (an increase of 2 or more points in the NIHSS score). Data obtained from our previous research as well as other domestic research showed that the rate of END on the third day after stroke onset was approximately 6–8%. The sample size was calculated on the following assumptions: the END rate in patients who did not receive the TCM intervention was 13% based on data from studies conducted overseas, and the END rate in patients who received the TCM intervention was 7% based on domestic data. Since there is no formula meant specifically for calculating the sample size in registry studies, we decided to use the one-sided difference test based on the statistical analysis method and formula for calculating the sample size in cohort studies. Consequently, the following formula, where α = 0.05 and β = 0.2, was used:
$$\text{n}={\left[\frac{Z_{1}-\alpha \sqrt{2\text{pq}}+Z_{1}-\beta \sqrt{{\text{p}}_{1}\left(1-{\text{p}}_{1}\right)+{\text{p}}_{2}\left(1-{\text{p}}_{2}\right)}}{{\text{p}}_{1}{-\text{p}}_{2}}\right]}^{2}.$$

The smallest sample size for a single cohort was estimated to be 426 patients; therefore, a minimum of 852 patients must be included. Considering the uneven distribution of exposure factors among patients and the inability of some patients to attend all the visits through the 90 days, the sample size was increased to 1,000 cases, which is an increase of 17% on the original base size.

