### Data processing and analysis

The mean (Mean), standard mean difference (SD), median (Median), interquartile ranges, minimum (Min), and maximum (Max) will be used to summarize continuous data, while rate or percentage will be used for categorical data. Between-group comparisons will be conducted using parametric or non-parametric tests, as appropriate. Pearson’s chi-squared test is used for the count data, and the results are expressed as rate or percentage (%). Measured data, if data are normally distributed and the variance is homogeneous, the parametric test (*t*-test) will be used and results will be expressed as mean ± SD; If the data are not normally distributed and still do not meet the requirements for the parametric test after data conversion, the non-parametric test (Wilcoxon rank sum test or Mann-Whitney U test) will be used and results will be expressed as median (Median).

As the primary analysis, a comparison of the presence of END on the third day after stroke onset will be conducted between the two groups of patients—the exposure group and the nonexposure group—using Pearson’s chi-squared test. The secondary outcome analyses will involve the rate of stroke-related and any-cause deaths, differences in the NIHISS scores, differences in the ICH scale scores, proportion of patients with BI scores ≥90, and proportion of patients with mRS scores ≤2. These analyses will be performed according to the standard statistical principles for comparing parametric or non-parametric distributions, as appropriate. During the analysis, multivariate linear regression analysis is performed for the influencing factors that are statistically significant in the univariate analysis. The full analysis set will be used in the efficacy correlation analysis in this study. The safety analysis set will be used in the safety analysis. The full analysis set refers to the set of eligible cases and detached cases but not eliminated cases. The safety analysis set will consist of safety indicators for all enrolled subjects with post-medication safety evaluation data; the number of subjects with missing data will be reported. All statistical tests will be one-sided, and statistical significance will be set at *p* < 0.05. SAS software, version 9.2 (SAS Institute, Inc., Cary, NC, United States), will be used to perform the statistical analyses.

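### The primary END comparison is fixed as one unstratified test across ischaemic stroke and ICH, which leaves it open to confounding by stroke type and can hide no effect or harm in one type

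*Protocol article*

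**What the plan says.** The Abstract sets the population: "we aimed to recruit 1,000 patients with acute stroke (IS and ICH"). Under Efficacy outcomes the primary outcome is the same for both types: "END on the third day of onset defined as an increase of 2 or more points in the NIHISS score between baseline and day 3".

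In the section Data processing and analysis, the main test is set out as follows: "a comparison of the presence of END on the third day after stroke onset will be conducted between the two groups of patients", that is, exposed against nonexposed, "using Pearson’s chi-squared test". The same section makes all tests one-sided at 0.05. Its only regression is described thus: "multivariate linear regression analysis is performed for the influencing factors that are statistically significant in the univariate analysis". Stroke type is not named there.

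The Sample size calculation uses one END rate per exposure group (13% and 7%) for both types together. It opens with the premise that "at least one particular subgroup will have a positive outcome in terms of the primary efficacy index", but does not define that subgroup or attach an analysis to it.

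Type is available. CT or MRI is used to reject patients without acute stroke and is recorded at Visits 2 and 4, and the discharge diagnosis is recorded (Table 1). Table 1 also lists different major treatments for the two types: thrombolysis and endovascular treatment for ischaemic stroke, surgery and others for ICH.

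**The concern.** Two separate problems follow from a crude test in this cohort.

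- **Confounding by type.** Clinicians decide who receives XNJI. If exposed and nonexposed patients differ in their share of ICH, and END is more or less common in ICH, the crude comparison mixes the type difference with the XNJI effect. The error can go in either direction.
- **Averaging.** Even with equal shares, one pooled difference is a weighted mean of two type-specific effects. Benefit in the larger group can cover no effect or harm in the smaller. A one-sided test does not look for harm.

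At stake is how the result is read. A positive pooled finding for acute stroke could be taken as benefit in ICH when the data for ICH show none.

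**Working it through.** **Inputs.** END 13% nonexposed and 7% exposed, one-sided 0.05, total 1,000 (Sample size calculation; Data processing and analysis). Type mix from the Introduction: "ischaemic stroke (IS) had a prevalence of 62.4%, and intracerebral brain hemorrhage (ICH), of 27.9"%. Rescaled to these two types, the IS share is 62.4/(62.4 + 27.9) = 0.691 and the ICH share 0.309. This is a background figure, not the trial's own mix. Assumptions: 500 per group, and ICH END rates of 13% or 20% without XNJI. The article gives no END rate by type.

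**The plan's own figure.** The printed formula with α = 0.05 one-sided and β = 0.2 gives 308.1, so 309 per group, not the stated 426. With β = 0.1 it gives 426.3. This does not affect the present point, because everything below uses 500 per group.

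**Power formula.** Φ{[d − 1.645·√(2p̄(1−p̄)/n)] / √[(p₁(1−p₁) + p₂(1−p₂))/n]}, with n = 500.

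*Same effect in both types:* d = 0.06, p̄ = 0.10. Power = Φ[(0.0600 − 1.645 × 0.0190)/0.0189] = 94%.

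**Averaging, with the same mix in both groups.** The IS effect is 13% to 7% throughout.

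| ICH nonexposed → exposed | Pooled nonexposed | Pooled exposed | Difference | Power |
|---|---|---|---|---|
| 13% → 13% | 13.0% | 8.9% | 4.1 | 68% |
| 20% → 20% | 15.2% | 11.0% | 4.1 | 62% |
| 13% → 19% | 13.0% | 10.7% | 2.3 | 30% |
| 20% → 26% | 15.2% | 12.9% | 2.3 | 27% |

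Example, last row: 0.691 × 13 + 0.309 × 20 = 15.2 and 0.691 × 7 + 0.309 × 26 = 12.9. The pooled sign favours XNJI although ICH is worse by 6 points.

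*Range over the mix:* with ICH at 15% or 50% of patients, the IS-only difference is 0.85 × 6 = 5.1 or 0.50 × 6 = 3.0 points. The harm scenario gives 5.1 − 0.9 = 4.2 or 3.0 − 3.0 = 0 points.

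**Confounding, with no XNJI effect in either type.** Assume END 10% in IS and 20% in ICH, with ICH forming 20% of exposed and 40% of nonexposed patients.

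- Exposed: 0.8 × 10 + 0.2 × 20 = 12%.
- Nonexposed: 0.6 × 10 + 0.4 × 20 = 14%.
- Rejection probability: Φ[(0.020 − 1.645 × 0.0213)/0.0213] = 24%, against a nominal 5%.

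With a milder imbalance (25% against 37%) the rates are 12.5% and 13.7% and the test rejects 14% of the time. An imbalance the other way would bias against XNJI.

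**Precision by type.** Half-width = 1.96·√[(p₁(1−p₁) + p₂(1−p₂))/n].

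- IS, about 345 per group, 13% and 7%: 4.5 points.
- ICH, about 155 per group: 6.7 points (13% and 7%), 7.5 (13% in both), 8.9 (20% in both), 9.4 (20% and 26%).
- Two-sided power of the exposure-by-type interaction: 22–27% if ICH is unaffected, 62–72% if ICH is harmed by 6 points.

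**The case against.** The strongest reply is that the pooled comparison fits the question. Inclusion is on suspected stroke, XNJI is given in the ambulance, and imaging comes after admission. The average effect over the mixed population that crews meet is a coherent quantity, and the article claims only preliminary evidence. This stands. A reader might infer that enrolling or pooling both types is itself an error; the documents do not support that.

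Second, by-type tables and interaction tests are often left to the analysis plan, which is not shown. This also stands. A reader might infer that no type-specific analysis is planned, or that mRS, Barthel Index and mortality will never be shown by type. All that can be said is that this article states no END estimate by type. The crude primary test is different, because the article fixes it.

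Third, stroke type could enter the regression. It could, but only if it passes a univariate screen, and then in a linear model outside the named primary test.

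Fourth, the type-specific inputs are assumed. That is correct: the documents give neither END rates nor XNJI effects by type, so they do not show that XNJI acts differently in ICH, still less that it harms. Nor does Table 1 show wholly opposite treatment. It separates the major treatments by type but lists haemostatic agents among general in-hospital medication.

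**Conclusion.** The point holds for the primary test as stated. In a non-randomised cohort, an unstratified test across IS and ICH is exposed to confounding by type, and its single one-sided result can conceal no effect or harm in one type. Under the 69/31 mix, 500 per group and assumed ICH rates, power falls from 94% to 62–68% if only IS benefits, and a 6-point ICH harm appears as a 2.3-point benefit. Under the assumed 20%/40% imbalance in ICH share, false rejection is about 24%. These figures illustrate the mechanism and do not predict the trial's result; actual mix, rates and group sizes will move them.

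The weakness should be corrected but does not invalidate the design. The pooled estimate remains usable as an average, provided benefit in each type is not claimed from it alone.

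**What to change.** 1. Make the primary END comparison stratified by imaging-confirmed type: a Mantel-Haenszel risk difference, or a logistic model with a type term alongside the other confounders. This deals with confounding by type. It does not deal with averaging, because a Mantel-Haenszel estimate is still one weighted mean.
2. Beside it, report the END risk difference with a two-sided 95% CI separately for IS and ICH, with the exposure-by-type interaction as descriptive support. This deals with averaging.
3. Label the overall estimate as the average effect in the mixed prehospital population, and state that benefit in each type will not be claimed from it alone.

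The cost is analysis wording and a few tables; the data are already collected. The drawback is precision: the ICH half-width is about 7 to 9 points, wider than the planned 6-point effect, and the interaction test is weak. Estimates and intervals should therefore carry the conclusion, and no pass/fail rule on whether the two types agree should be used.

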### Intervention measures

The quantitative research part of this study will be observational. Based on our observation of whether XNJI was intravenously administered within 24 h of onset in the prehospital ambulance setting, patients with acute stroke will be divided into two groups: the exposure group comprising patients who were intravenously administered XNJI and the nonexposure group comprising patients who were not. During the study period, all relevant data will be collected at the following timepoints to facilitate a continuous dynamic observation and evaluation: during the prehospital ambulance service; within 24 h of admission; day 3 after stroke onset; day 10 after stroke onset or the day of discharge; and 30 ± 3, 60 ± 3, and 90 ± 7 days after stroke onset. This research will not interfere with the actual diagnosis and treatment of the participants. The clinicians will make decisions regarding routine treatment options based on the patient’s specific circumstances. The routine stroke treatment will follow the current national guidelines for acute Is and ICH from the Chinese Society of Neurology.

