TOAST classification of AIS	Major artery Atherosclerotic stroke; Cardiogenic cerebral embolism; Arterial occlusive stroke or lacunar stroke; Ischemic stroke resulting from other causes; Unknown cause of ischemic stroke
Major treatment methods	IVT and EVT for AIS; Surgery (craniotomy hematoma removal; minimally invasive surgery; bone valve decompression; ventricular drainage) and others for ICH
In-hospital medication	Antihypertensive agents; Hypoglycemic agents; Lipid-lowering drugs; Anticoagulants; Hemostatic agents; Reduced cranial pressure agents; Anticoagulants agents; XNJI (start use time; stop use time; use frequency; administration duration time; dose); Other TCM (Chinese patent medicine injection agent; Chinese patent medicine oral agent; TCM soup agent)
In-hospital rehabilitation	Acupuncture and moxibustion; Massage; PT; OT; ST; Others
Auxiliary examination	Vital signs; Laboratory tests; Cranial CT or MRI; ECG
Complication	Lung infections; Urinary tract infections; Upper gastrointestinal bleeding; Hiccups; Dysphagia; Urine retention; Urinary incontinence; Pressure ulcers; Kidney failure; Pulmonary embolism; Epilepsy; Shoulder-hand syndrome; Post-stroke depression; Post-stroke anxiety; Others
Indicators on health economics	Hospitalization costs; Treatment costs; Inspection fees; Medicine costs; Other costs; Total costs; Number of days of hospitalization
Discharge diagnosis	
In-hospital mortality	
Discharge evaluation	NIHSS; ICH Scale and GCS for ICH
Visit 5 (day 30 ± 3 after symptom onset)	
Follow-up evaluation	mRS; BI
Visit 6 (day 60 ± 3 after symptom onset)	
Follow-up evaluation	mRS; BI
Visit 7 (day 90 ± 7 after symptom onset)	
Basic medication	Antithrombotics agents; Anticoagulants agents; Lipid-lowering drugs; Antihypertensive agents; Hypoglycemic agents; TCM
Rehabilitation	Acupuncture and moxibustion; Rehabilitation exercise
Follow-up evaluation	mRS; BI
AEs (during the observation period)	Start time; Symptoms/signs; Intensity; Attack frequency; Duration and termination time; Laboratory indicators; Treatment methods and outcomes; Follow-up results

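### The only adjusted analysis is a linear regression with covariates screened by univariate p-value: it does not suit the binary outcomes, or else leaves END unadjusted, and the screen can drop real confounders

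*Protocol article*

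**What the plan says.** The exposure is observed, not assigned. Under Intervention measures the article states: "This research will not interfere with the actual diagnosis and treatment of the participants". Who receives XNJI in the ambulance therefore depends on routine care.

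The Efficacy outcomes section makes END a yes/no endpoint, "defined as an increase of 2 or more points in the NIHISS score between baseline and day 3". Under Data processing and analysis, the primary analysis is an unadjusted Pearson chi-squared test: "As the primary analysis, a comparison of the presence of END on the third day after stroke onset will be conducted". The secondary outcomes there are of two kinds. Deaths and "proportion of patients with BI scores ≥90, and proportion of patients with mRS scores ≤2" are binary; "differences in the NIHISS scores, differences in the ICH scale scores" are changes in a score.

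One sentence on adjustment follows: "multivariate linear regression analysis is performed for the influencing factors that are statistically significant in the univariate analysis". It names no dependent variable. No logistic or other binary-outcome model appears in the article, and it singles out no confounder. Table 1 lists variables recorded after the ambulance phase, including day-3 complications, in-hospital XNJI and major treatments ("IVT and EVT for AIS; Surgery" and others).

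**The concern.** With exposure left to routine care, patients given XNJI may differ from the others in severity, stroke type or time since onset. The regression sentence is the only step in the article that deals with this, so its content matters.

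Three things in it are doubtful:

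- **Model.** A linear model is natural for a change in NIHSS, but not the usual choice for a binary outcome with an expected rate near 10%.
- **Selection.** A p-value against the outcome does not identify a confounder. A variable confounds through its links with both exposure and outcome, and with about 100 events many real predictors will not reach significance.
- **Candidates.** The factors eligible for the model are not limited to those present before XNJI was given. Adjusting for a consequence of exposure can remove part of an effect or create bias.

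At stake is whether any adjusted END estimate exists and, if so, whether it can be trusted as a check on the crude comparison.

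**Working it through.** The article gives no figure for this step, so there is none to reproduce. Two calculations show its size.

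**1. Standard error of a linear model for END**

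Inputs from Sample size calculation: END 7% exposed, 13% non-exposed, N = 1,000. The exposure split is an assumption; that section says only that exposure will be uneven.

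Binomial variances: 0.07 × 0.93 = 0.0651 (exposed) and 0.13 × 0.87 = 0.1131 (non-exposed).

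- Model-based: SE = √[s²(1/n₁ + 1/n₀)], with s² = (n₁ × 0.0651 + n₀ × 0.1131)/N
- Correct: SE = √[0.0651/n₁ + 0.1131/n₀]

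| Exposed / non-exposed | s² | Model-based SE | Correct SE | Ratio |
|---|---|---|---|---|
| 200 / 800 | 0.1035 | 0.0254 | 0.0216 | 1.18 |
| 500 / 500 | 0.0891 | 0.0189 | 0.0189 | 1.00 |
| 800 / 200 | 0.0747 | 0.0216 | 0.0254 | 0.85 |

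The error comes from imbalance in exposure, not from the event rates alone.

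**2. Chance that the univariate screen misses a true confounder**

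Assumptions, none from the documents: a binary factor with prevalence 20% or 30%, overall END 10%, odds ratio as shown, N = 1,000, screening at 0.05. The 10% is the 1:1 average of 7% and 13%.

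Power = Φ{[(p₁ − p₀) − z × SE₀]/SE₁}, where SE₀ uses the pooled 10% and SE₁ the two separate risks.

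Worked case, prevalence 20% and odds ratio 1.5:

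- Risks are 9.2% and 13.2%, a difference of 0.0399 before rounding.
- SE₀ = √[0.1 × 0.9 × (1/800 + 1/200)] = 0.0237; SE₁ = 0.0260.
- One-sided (z = 1.645): power 0.514, missed 49%.
- Two-sided (z = 1.960): power 0.401, missed 60%.

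| Odds ratio | Missed at 20% prevalence (one- / two-sided) | Missed at 30% prevalence (one- / two-sided) |
|---|---|---|
| 1.3 | 71% / 80% | 67% / 77% |
| 1.5 | 49% / 60% | 42% / 54% |
| 2.0 | 12% / 18% | 7% / 12% |

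**3. What a missed confounder does to the estimate**

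A simulation of 1,500 studies took no true XNJI effect, 500 patients per group, and a single confounder present in 40% of exposed and 20% of non-exposed patients. It used logistic models and a chi-squared screen. The true exposure odds ratio is 1.00.

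| Confounder odds ratio | Crude | Screened | Prespecified |
|---|---|---|---|
| 1.5 | 1.10 | 1.04 | 1.01 |
| 2.0 | 1.17 | 1.02 | 1.01 |

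On average, screening leaves part of the bias, but little from one such factor. Several confounders or stronger imbalance would leave more.

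**4. Candidate variables**

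Set beside Table 1, the regression sentence excludes nothing. Complications at day 3, thrombolysis or endovascular treatment, surgery, in-hospital XNJI and rehabilitation all follow the ambulance phase. Any that is associated with the outcome would meet the stated entry rule.

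**The case against.** The strongest reply is that the sentence may concern only the NIHSS and ICH-score changes listed just before it, where a linear model is defensible. That stands: a reader might infer that the plan prescribes linear regression for END, but the text does not say so. It does not rescue the plan, because END would then have no adjusted analysis in the article. A linear model for a binary outcome can also be a deliberate risk-difference analysis with robust errors; nothing indicates that this is meant.

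Other strong inferences also fail:

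- **That the standard errors are simply invalid at rates of 7–13%.** They are correct at 1:1, and the documents do not give the exposure split.
- **That the article's one-sided rule bars any factor acting in the untested direction.** Pearson's chi-squared test, which the article names for count data, has no direction, and no direction is stated for any covariate.
- **That the trial plans to adjust for post-exposure variables.** Table 1 lists what is recorded, not what enters a model. The wording leaves this open and no more.

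It is also fair that a full covariate list commonly sits in a statistical analysis plan. The absence of a list is not the point here; the fault is a selection rule that the article does state. Finally, the primary analysis is the unadjusted test, so repairing the regression does not by itself adjust the headline result.

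**Conclusion.** The point holds in this form. The article fixes one multivariable model and one selection rule as its only control of confounding, and both are poorly chosen for a non-randomised study whose primary and most secondary outcomes are binary.

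The size of the model fault depends on the exposure split: none at 1:1, and from about 18% too large to 15% too small between 20/80 and 80/20. The screen misses a confounder of odds ratio 1.5 about 42–60% of the time and one of 2.0 about 7–18%. These ranges rest on the assumed prevalence of 20–30%, 10% END and N = 1,000, and span one- and two-sided screening. A reader might take the miss rates as a measure of bias; they are not, and in the single-confounder illustration the exposure odds ratio after screening was at most 1.04 against a true 1.00. Entry of post-exposure variables is a gap in the wording, not a stated plan.

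It should be put right before analysis, since the remedy needs no new data.

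**What to change.** Rewrite the regression sentence so that it:

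- **names the outcomes and models:** logistic regression, or modified Poisson with robust standard errors if risk ratios are wanted, for END, death, BI ≥90 and mRS ≤2; linear or ANCOVA models only for NIHSS and ICH-score change;
- **drops the univariate screen** and enters a short prespecified list regardless of p-value, for example age, sex, prehospital NIHSS, state of consciousness, ischaemic stroke or ICH, onset-to-ambulance time, prior stroke, atrial fibrillation and diabetes. All are in Table 1 or follow from data recorded there;
- **handles hospital** by a random effect, stratification or clustered standard errors. With the 20 sites given under Recruitment, a fixed factor would cost 19 parameters;
- **keeps variables arising after ambulance exposure** (complications, in-hospital treatments, rehabilitation) out of the main model.

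The nine covariates above, one term each, plus exposure make 10 parameters. Expected END events at 1:1 are 500 × 0.07 + 500 × 0.13 = 100, or 10 per parameter; splits from 20/80 to 80/20 give 118 to 82 events. Adding 19 hospital terms would make 29 parameters, about 3.4 events each at 1:1.

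The cost is protocol and analysis-plan wording. Data collection and sample size do not change.
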